### 3.1.2 Research areas and direction:

### Public Health

###

### Within the project section it is intended to:

- carry out research on human subjects  Yes  No
  A copy of the required approval of the responsible ethics committee is included
- conduct clinical studies in
  somatic gene therapy  Yes  No
- conduct experiments involving animals  Yes  No
- conduct experiments involving
  recombinant DNA  Yes  No
- carry out research with human embryonic
  stem cells  Yes  No
- The legal authorisation has been obtained  Yes  No

## 3.2 Summary

The hypothesis that insecticide-treated bed net (ITN) effects may not be long-lasting in young children living in areas of intense malaria transmission due to interactions with the immunologi-cal development has now been refuted in a number of studies including the D4 study. The highly controversial question remains how African programmes can best reach a sustainable high coverage with ITNs in young children and pregnant women. Against this background it is planned to implement a cluster randomised controlled trial in Nouna Health District in Burkina Faso. Twenty-two peripheral health centres and their catchment areas will be randomised to (1) ITN provision to the general population through social marketing and (2) ITN provision to the general population through social marketing plus free provision to all pregnant women through antenatal services. The primary outcomes are ITN coverage in households and ITN use during pregnancy and infancy.

**Zusammenfassung**

Die Hypothese, dass Insektizid-behandelte Mosquitonetze (ITN) bei Kleinkindern in Gebieten hoher Malariaendemizität langfristig nicht effektiv sein könnten, wurde in den letzten Jahren von verschiedenen Studien einschliesslich der D4 Studie widerlegt. Als hochkontrovers diskutiertes Thema bleibt allerdings die Frage, wie am besten auf Programmebene ein nachhaltig hoher Schutz mit ITN für Kleinkinder und schwangere Frauen in afrikanischen Malariagebieten erreicht werden kann. Vor diesem Hintergrund planen wir eine Gruppen-randomisierte kontrollierte Studie im Nouna Gesundheitsdistrikt in Burkina Faso. Es ist eine Randomisierung des Einzugsgebietes von 16 ländlichen Gesundheitsstationen vorgesehen zu (1) Ausgabe von ITN an alle schwangeren Frauen über Schwangerenvorsorge-Dienste und (2) ITN Ausgabe an die Allgemeinbevölkerung über ein Social Marketing System. Hauptendpunkte der Studie sind die Versorgung der Haushalte mit ITN und die Benutzung von ITN während der Schwangerschaft und zum Schutz der Säuglinge und Kleinkinder.

## 3.3 Report on the development of the project section thus far

##

## 3.3.1 Report

**Scientific background for studies during phase 1 and 2 of SFB 544**

## Insecticide-treated nets (ITN) and particularly mosquito nets as a new tool in malaria control have received considerable interest over the last two decades. During the 1980s, a number of small-scale studies with synthetic pyrethroid insecticides have demonstrated significant reductions in malaria morbidity associated with ITN use in different African, Asian and Latin-American populations (Lindsay & Gibson 1988; Rozendaal 1989; Bermejo & Veeken 1992). Subsequently, a number of large randomised-controlled ITN efficacy and effectiveness trials have been conducted during the 1990s in sub-Saharan Africa (SSA). These trials have consistently demonstrated the efficacy and partly also the effectiveness of ITNs in reducing malaria morbidity and mortality over a broad range of malaria transmission intensities (Lengeler 1998; Phillips-Howard *et al.* 2003). However, as all these trials were only designed for short intervention periods, the long-term consequences of particularly young children’s protection from malaria through ITNs were not known. The value of using such an intervention in areas with high malaria transmission intensity had been discussed very controversially in the recent past. The major scientific questions regarding the use of ITNs for the protection of young children concerned the interaction between passively acquired immunity and ITN use during the first months of infancy as well as a possible shift of malaria morbidity and mortality to older age groups (Snow et al. 1995, Trape et al. 1996, Snow et al. 1997, Alles 1998). The debate remained controversial over the following years with various publications on this subject (Mondiano et al. 1998, Beier et al. 1999, Thomas & Lindsay 2000; Smith et al. 2001, Mathanga & Molyneux 2001, Armstrong Schellenberg et al. 2001, Coleman et al. 2001, Abdulla et al. 2001, Binka et al. 2002, Maxwell et al. 2002).

#### *Study-objectives, design and methods*

The main objective of the D4 trial was to determine differences in the rates of malaria morbidity and mortality as well as all-cause mortality in children protected with ITNs from birth up to their fifth birthday (group A) compared to children protected with ITNs from month seven up to their fifth birthday (group B) in a holoendemic area of West Africa.

The study was designed as an individually randomized controlled ITN community trial (n=3.400). Newborn children were recruited for the study from June 2000 until December 2002 from all 39 villages of the study area of the Centre de Recherche en Santé de Nouna (CRSN) in Nouna Health District in north-western Burkina Faso. Mothers and their children were provided at the time of delivery (group A) or after six months (group B) with deltamethrin-treated mosquito nets (PermaNet) through field staff regularly visiting the study villages. The primary study endpoints were all-cause mortality in cohort children measured through the existing demographic surveillance system (DSS) of the Nouna Health Research Centre in the study region, and malaria morbidity measured through bi-annual cross-sectional surveys and longitudinal follow-up of malaria incidence in sentinel villages.

### *Results*

- In preparation for this study, a survey of traditionally existing mosquito net coverage in the study area has been carried out in 1998. Around 35% of households were reporting ownership of at least one mosquito net, with high heterogeneity with regard to village and ethnic background (Traoré et al. 2002, Traoré 2003).
- Qualitative and quantitative anthropological research carried out during 1999 has guided the selection of mosquito nets for the ITN trial. The majority of mothers preferred rectangular big size synthetic bed nets of dark colour. Thus the project has bought rectangular family-size dark-green mosquito nets, pre-impregnated with Deltamethrin (first generation PermaNet) (Müller et al. 2002).
- An anthropological study on community factors associated with malaria prevention by mosquito nets revealed traditional concepts and practices in the Nouna area. Mosquito nets were confirmed to be prevalent in the villages, but mainly used by adults against mosquito nuisance (Okrah et al. 2002).
- In the research zone of the Nouna Health Research Centre, malaria in young children is mainly caused by *P. falciparum*. The transmission intensity is high and seasonal, reaching several hundred infectious bites per person per year, but with major differences between villages (Traoré 2003, Müller 2001, Müller et al. 2001)
- Corresponding childhood mortality and malaria-specific mortality is high in the area, with again major differences between villages (Sankoh et al. 2001, Müller et al. 2003a). Anaemia is the major manifestation of severe falciparum malaria in the study area, with malnutrition being an important co-factor (Müller et al. 2003b).
- Most fever/malaria treatment in the Nouna research zone is home treatment with chloroquine, antipyretics and traditional remedies (Müller et al. 2004a, Müller et al. 2003c).
- Resistance against chloroquine, the first-line treatment for uncomplicated malaria, is already prevalent in the CRSN study area (Müller et al. 2003d). In contrast, pyrimethamine-sulfadoxine is still sufficiently effective (Müller et al. 2004b)
- Results from a joint study of SFB 544 groups A1 and D4 are pending. Serum samples were collected over a period of 12 months from 120 infants of the D4 study in 2001/2002. These sera are currently processed in Heidelberg with a specific gp190 ELISA developed by [name].

**Scientific background for studies planned during phase 3 of SFB 544**

ITNs were already employed on a large-scale since the 1980s in many malaria endemic areas of Asia, where they have contributed to major successes in malaria control (Hung *et al.* 2002). Today, the need for a large scale introduction of ITNs in SSA is well accepted in the scientific community as well as among international agencies (Curtis *et al.* 2003; Lines *et al.* 2003; Whitty *et al.* 2002; Hawley *et al.* 2003; WHO 2002). A high coverage with ITN would also lead to a mass effect on the mosquito populations similar to what can be achieved through systematic insecticide spraying programmes (Binka et al. 1998, Ilboudo-Sanogo et al. 2001, Maxwell et al. 2002). However, due to major differences in infrastructure, public service organisation, funds and epidemiology, progress in the implementation of ITN intervention in SSA was slow (Victora et al. 2004). Today, only some 2% of children in SSA are protected with ITN (WHO 2003).

So what is the best strategy for scaling-up ITN coverage in SSA? Two approaches – often seen as incompatible – are competing with each other in the international debate. The first group argues to consider ITN as a public good like vaccines and to consequently provide them through the public sector free of charge, while the second group argues for strengthening commercial markets but acknowledges the importance of subsidies for the groups most at risk (e.g. pregnant women and young children) (Curtis *et al.* 2003; Lines *et al.* 2003). The group in favour of free ITN distribution and re-treatments supports their argumentation by the evidence from a few east African pilot projects regarding the feasibility of such an approach, the existence of a significant community effect in most areas with high ITN coverage, the reality of a high proportion of the rural populations in SSA being unable to pay for such an intervention, and the hope that rich countries would be willing to pay for malaria control in SSA (Curtis *et al.* 2003). On the other side, the group in favour of strengthening commercial markets supports their argumentation by the success of a large ITN social marketing programme in rural Tansania (Armstrong-Schellenberg *et al.* 1999; Hansen *et al.* 2003; Mushi et al. 2003), the important role of market involvement in the success of ITN programmes in Asia, the assumption that free ITN provision would destroy local commercial markets, and the uncertainty of a continuous availability of external funds for ITN programmes. There is however considerable agreement in both groups regarding the need for major donor assistance for whatever approach (e.g. through the Global Fund for AIDS, malaria and Tb) (Curtis *et al.* 2003; Lines *et al.* 2003).

What is the evidence for providing pregnant women and subsequently their young children with free ITN and free re-treatment being feasible and effective. Initial evidence for this stems from the Gambian National Impregnated Bednet Programme (D`Alessandro *et al.* 1995). During the first year of this programme villagers were offered insecticide free of charge through their respective village health workers, while during the second year the insecticide was started to be sold at a prize of some 0.5 USD. The introduction of fees for service was accompanied by a sharp drop in impregnation coverage from 85% during the first year to only 14% in the second year (D`Alessandro *et al.* 1995; Cham *et al.* 1997). Cost-recovery was introduced into the whole country during the third year of the programme, and communities were offered insecticide again through village health workers but alternatively also through shops. In addition, women attending selected mother and child health (MCH) services were offered insecticide free of charge. An evaluation of the activities of the national programme during its third year provided evidence for offering insecticide through private channels leading to increased impregnation coverage, as well as for the provision of insecticide through MCH services being effective in targeting young children (Müller *et al.* 1997). These findings are furthermore supported by our experience from the ongoing D4 ITN trial in rural Burkina Faso, where all newborns and their mothers have been provided with free ITN and free annual re-impregnation (Müller *et al.* 2003e). This trial is now into its fourth year and coverage and re-impregnation rates have remained above 90%. As reported from other pilot projects with free provision of ITN, we also have no indication for ITN being sold or diverted (Curtis *et al.* 2003).

## 3.4 Planned continuation of the project section (objectives, methods, work programme)

**3.4.1 Aims**

**3.4.2 Methods**

Study design and definition of the intervention

This is a proposal for a community-based randomised controlled trial (RCT) with peripheral health centres (n=22) and their target villages as the units of randomisation. The catachment areas of the 22 health facilities will be randomised to receive either (1) ITN provision to the general population through social marketing (intervention A) or (2) ITN provision to the general population through social marketing plus free ITN provision to all pregnant women through antenatal services (intervention B). The National Malaria Control Programme (NMCP) is currently considering to shift its policy from one based exclusively on subsidised sales and social marketing to one which integrates free distribution among high-risk populations (i.e. pregnant women and young children).

Following a series of meetings in September 2005, it appears that the distribution of the ITNs will be secured by collaborative efforts between the NMCP, Population Services International (PSI), UNICEF, the Nouna Health District, the Nouna Health Research Centre (CRSN), and the Department of Tropical Hygiene and Public Health at the Heidelberg University (ATHÖG). Third generation PermaNet will be provided in both arms of the intervention.

Study outcomes

*Primary outcomes:* (1) ITN coverage in households 12 and 24 months after the start

of the interventions

(2) ITN use during pregnancy and infancy

*Secondary outcomes:* (1) Costs per malaria case and per DALY prevented

(2) Self-reported information on ANC visits

(3) Insecticide content on ITN and mortality of vector mosquitoes over time

(4) Acceptance of health staff and population

Sample size

The sample size calculation is based on the primary outcome ITN coverage. In order to demonstrate a 15% difference and applying the design factor 2 for clustering, the required sample size will be 400 households per study arm. In order to compensate for migration and possible loss in follow up, 500 households will be enrolled in each arm.

Study methods

By using standard two-stage EPI cluster sampling methodology, 500 randomly sampled households from the intervention A and 500 randomly sampled households from the intervention B area will be visited before the start of the intervention (February 2006). New random samples will be drawn again after 12 months and 24 months respectively. ITN coverage will be measured through self-reported information on a standardised questionnaire and through direct observation. ITN use during pregnancy and infancy will be measured through self-reported information on a standard questionnaire. These data will be validated through direct observations during the rainy season of 2007 in a sub-sample of 100 households in the study area. These households will be also part of the survey sample of January 2008.

Costing estimates and cost-effectiveness calculations will be undertaken in close collaboration with [name]. [name], University of Greifswald. [name] has been a member of the Department of Tropical Hygiene and Public Health at the Heidelberg University until recently and is working on the costing of health interventions in Nouna. The current funding period of the SFB 544 has let project D7 in and [name] will continue to work on costing of health intervention aspects in Burkina Faso after his move to Greifswald.

Random samples of 100 ITN will be taken at the time of the third household survey follow up in 2008, for determination of deltamethrin content using xylene extraction and capillary gas chromatography. In addition, ITN efficacy will be measured using standard WHO bioassays with the endpoint of mosquito mortality 24 hours after three minutes exposure to the ITN. The ITN washing frequency will be recorded.

Community perceptions regarding the different ITN distribution channels will be studied with qualitative methods (focus group discussions, individual interviews and key informants interviews) during the intervention phase (rainy season 2007).

Study site

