- Distribution of ITNs free of charge to all pregnant women through the health centre-based ANC services of the intervention area A (starting in June 1st).
- Distribution of ITNs at a subsidised prize to the population through a shop-based distribution system in the frame of a PSI-supported social marketing approach (to be defined).
- Comprehensive data collection on process indicators (to be defined).
- Implementation of the costing study
- The first follow-up sample will be defined.
- Data entry, data cleaning.

During 2007, the following activities are planned:

- The second cross-sectional survey will be carried out in February after training of respective field staff and preparation of all materials.
- Knowledge, attitudes and practices (KAP) study in a random sample of the study population and in a provider sample (February/March/April).
- Continuation of distribution of ITNs free of charge to all pregnant women through the health centre-based ANC services of the intervention area A.
- Continuation of distribution of ITNs at a subsidised prize to the population through a shop-based distribution system in the frame of a PSI-supported social marketing approach.
- Continuation of data collection on process indicators and costing data.
- Validation study (on a sample of 100 households to be matched with the 2008 follow-up sample) on ITN use during pregnancy and infancy (August/September).
- The second follow-up sample will be defined.
- Data entry, data cleaning.

During 2008, the following activities are planned:

- The second cross-sectional survey will be carried out in February after training of respective field staff and preparation of all materials.
- The ITNs (100) for the entomological efficacy study sample will be collected during the second follow up survey (February). Laboratory tests to assess mosquito mortality will be conducted directly in Nouna by the two entomological assistants under the supervision of a professional entomologist to be contracted. Laboratory tests to assess insecticide content will be conducted by a specialised laboratory in Europe.
- Final data entry, data cleaning, data analysis, report writing.
- Presentation of study data to policy makers through a national workshop

Ethical considerations

The protocol has been reviewed and approved by the Ethics Committee of the University of Heidelberg and the local Ethics Committee in Nouna, Burkina Faso.

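### Use of nets in pregnancy and infancy has no time point and no birth or pregnancy window, and the first follow-up comes only about 8 months after free nets begin, so that reading can be pulled towards zero

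*Protocol*

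**What the plan says.** Section 3.4.2 (Study outcomes) lists two primary outcomes. The first carries time points: "1) ITN coverage in households 12 and 24 months after the start" of the interventions. The second is only "2) ITN use during pregnancy and infancy". The Study methods text adds that use is self-reported on a questionnaire, with direct observation in 100 households as validation. It gives no age limit, recall period or eligible pregnancies.

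Under Study design, the arms differ in one thing: free nets for pregnant women through antenatal services. Section 3.3.1 expects infants to be protected afterwards by sleeping under the mother's net.

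On timing, the work plan for 2006 has "Distribution of ITNs free of charge to all pregnant women through the health centre-based ANC services of the intervention area A (starting in June 1st". Baseline households "will be visited before the start of the intervention (February 2006", and "New random samples will be drawn again after 12 months and 24 months respectively". The work plan for 2007 says "The second cross-sectional survey will be carried out in February". The 2008 list repeats that sentence, while Study methods puts the last survey in January 2008.

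The work plan places free nets in area A, whereas Study design and the Summary place them in the second arm (intervention B). That needs reconciling too, but it does not affect the timing argument.

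**The concern.** A woman can receive the free net only while pregnant and only from 1 June 2006. An infant born before that date could not have been reached through the mother's pregnancy with that child. Nothing in the outcome excludes such infants, or pregnancies that had already ended, from the comparison at the first follow-up. They would enter both arms with no opportunity to differ through that pregnancy.

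Two things are at stake. The 2007 difference may look small because of birth dates rather than because the strategy failed. A larger difference in 2008 may then be read as a growing effect when part of it is the passing of births that predate the nets.

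**Working it through.** **The plan's own figure.** The only interval given is 12 and 24 months after the start. Counted from the February 2006 baseline, surveys in February 2007 and 2008 fit. Counted from 1 June 2006 they fall at about 8 and 20 months. The start of social marketing sales is left to be defined, but free nets are what separates the arms, so 1 June is the relevant date. The 400 households per arm belong to the coverage outcome and are not used here.

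**Inputs from the protocol.** Free nets from 1 June 2006; surveys in February 2007 and in January or February 2008.

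**Assumptions not in the protocol.** Infancy under 12 months; births uniform over the year; pregnancy of 9 months; a net available as soon as a woman is pregnant. Later antenatal attendance would worsen the 2007 figures.

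**Formulas.** Let S be months from 1 June 2006 to the survey and t the month of birth on the same scale, uniform from S - 12 to S.

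- Infants born before free nets: max(0, 12 - S)/12.
- Share of mothers' pregnancy time before free nets: mean of min(9, max(0, 9 - t)), divided by 9.

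Worked case, 1 February 2007 (S = 8): infants 4/12 = 33.3%. Pregnancy months before the start: 4 x 9 = 36 for births before June, plus the integral of (9 - t) from 0 to 8, which is 72 - 32 = 40. Total 76 out of 12 x 9 = 108, or 70.4%.

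| Survey | S | Infants born before free nets | Mothers' pregnancy time before free nets |
|---|---|---|---|
| 1 February 2007 | 8 | 33.3% | 70.4% |
| Mid-February 2007 | 8.5 | 29.2% | 66.6% |
| End February 2007 | 9 | 25.0% | 62.5% |
| 1 June 2007 (true 12 months) | 12 | 0% | 37.5% |
| 1 January 2008 | 19 | 0% | 1.9% |
| 1 February 2008 | 20 | 0% | 0.5% |
| 1 June 2008 (true 24 months) | 24 | 0% | 0% |

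**Dependence on who is asked.** For women pregnant on 1 February 2007, elapsed pregnancy time before 1 June is 0.5 out of 40.5, or 1.2%; by the end of February it is 0%. Pooling both groups gives (76 + 0.5)/(108 + 40.5) = 51.5% on 1 February and 67.5/148.5 = 45.5% at the end of the month.

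**By woman rather than by time.** In February 2007, 25-33% of mothers of infants had the whole pregnancy before 1 June, and 67-75% had at least some of it afterwards. For a survey on 1 February, 5/12 = 42% had three months or more after the start (births from September 2006).

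**Effect on a yes/no outcome in infants.** If infants born before 1 June showed no difference between arms, the all-infant difference would be 67-75% of that among later-born infants. This is conditional; the protocol gives no figure that fixes it.

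**The case against.** The strongest reply is that nothing makes the first follow-up the primary comparison, and by early 2008 the problem has practically gone. This stands. A reader might infer that the primary comparison as a whole is heavily diluted; the protocol does not support that, because only one of two follow-ups is affected. What remains is that no survey is named for this outcome, so the affected reading can count equally.

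Other stronger readings also fail:

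- A reader might take 70% as the attenuation. It is a share of time, at the worst end of the range, for mothers of infants recalling a whole pregnancy. Most of these mothers had some pregnancy time after the start.
- A reader might turn the 15% difference in the sample-size paragraph into 10 points (15 x 2/3). That 15% is for household coverage, and the step assumes zero effect in every infant born earlier. The protocol does not exclude a net arriving through another pregnant household member.
- A reader might think the problem independent of the survey date. For infants it is not: at a true 12 months the share born before free nets is 0%. For recalled pregnancy, 37.5% would remain.
- A reader might extend the figures to reported antenatal visits. No recall period is stated for that outcome, so no size can be given.

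Two further objections have weight. Slow arrival among children already born is a genuine property of antenatal distribution, so use in all infants is a legitimate population-level result and should be kept. Also, recall windows are often left to the questionnaire or SAP. Here, however, the protocol itself fixes the dates that create the overlap, and birth dates not collected cannot be recovered in the analysis.

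**Conclusion.** The point holds in a limited form. As scheduled, the first follow-up lets pregnancies that ended before the intervention count in a primary outcome. Under the stated assumptions this concerns 25-33% of infants and 62-70% of the recalled pregnancy time of their mothers, against about 0-1% for women pregnant at that survey and about 0-2% for mothers of infants in early 2008. The 2007 comparison can be pulled towards zero, and a rise to 2008 may be partly a matter of birth dates. The amount cannot be fixed from the protocol, which does not say who is asked or what effect is expected. The conflict between 12 and 24 months after the start and surveys at about 8 and 20 months is a plain inconsistency and produces the whole of the infant share.

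**What to change.** - Reconcile the survey dates with the stated 12 and 24 months after the start, and settle whether the last survey is in January or February 2008.
- Name the 2008 survey as the primary time point for use in pregnancy and infancy.
- Record each child's date of birth in the questionnaire, which the work plan has designed before the first survey.
- Count use in pregnancy only for pregnancies with time after 1 June 2006, or for current pregnancies, identically in both arms.
- For 2007, report infants born before and after 1 June 2006 separately, next to the figure for all infants.

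The cost is one date rule and one questionnaire item. The restricted 2007 comparison has fewer mothers and infants, about a quarter to a third fewer under the assumptions above. Moving the surveys alone would not be enough, since at a true 12 months 37.5% of the recalled pregnancy time of mothers of infants would still predate the nets.
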